#### Clinical assessments

To explore whether MBCT has an effect on motor symptom severity, we will test the effect of TIME (T0 vs. T1 vs. T2) and GROUP (MBCT vs. CAU) on MDS-UPDRS III scores in a linear mixed model (LMM) for repeated measures. We will also explore tremor amplitude as a function of GROUP (MBCT vs. CAU), TIME (T0 vs. T1 vs. T2) and CONDITION (rest vs. cognitive coactivation) using LMM. Similarly, bradykinesia scores derived by the key tapping task will be investigated as a function of GROUP and TIME. Further explorative analyses will test the effects of GROUP and TIME on cognitive abilities (MoCA), as well as self-reported psychological wellbeing and mindfulness skills (perceived stress, rumination, self-compassion, self-efficacy, positive appraisal style, mindfulness skills, social support and quality of life).

#### Behavioral assessments

We will use computational modeling to establish whether an actor or spectator model best explains a patient’s response patterns in a controllability update task. Specifically, from the behavioral data, a parameter is derived that captures the relative explanatory value of the actor and spectator model in the data. If the explanatory value of the actor model is larger than the spectator model, an environment is perceived as controllable. We will compare this parameter as a function of GROUP (MBCT vs. CAU) and TIME (T0 vs. T1 vs. T2).

#### Laboratory measurements

To explore whether MBCT influences biochemical markers of stress, the area under the curve with respect to increase [48] of *salivary cortisol* secretion pre- until 60 min post stress induction will be assessed as a function of TIME (T0 vs. T2) and GROUP (MBCT vs. CAU), while considering relevant covariates, such as age and gender. The predictive value of e.g. HADS at T0 and disease duration on the cortisol response will be explored using LMM. Similarly, changes in *hair cortisol levels* will be compared between T0, T1 and T2, and GROUP by means of LMM. To test the effect of MBCT on inflammatory tone (*hs-CRP*), causal mediation analysis techniques will be used to decompose causal effects of stress on neurodegeneration into four components: mediation (by inflammation) only, interaction (with inflammation) only, both, or neither.

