### Objectives

The primary objective of this study is to investigate whether MBCT in addition to care as usual (CAU), compared to CAU only, can reduce symptoms of anxiety and depression in people with PD, who experience mild to moderate levels of such symptoms at baseline. We consider anxiety and depression as severe stress symptoms and indicators of a maladaptive stress-response, resulting from enhanced or chronic levels of stress [7]. Our secondary objectives are to investigate whether the provided intervention (1) has an effect on motor symptom severity, (2) influences cerebral and biochemical markers of stress, and (3) changes biomarkers of PD progression.

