**Laboratory measures**										
Scalp hair cortisol		X		X						X
High sensitivity C-reactive protein		X		X						X
Salivary cortisol		X								X

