#### Laboratory measurements

*Scalp hair cortisol* will be collected to assess chronic stress in the preceding two months. Hair will be collected of subjects with a hair length of at least 3 centimeters. Analysis will be performed by the Radboudumc laboratory for diagnostics (RLD).

*High sensitivity C-reactive protein (hsCRP)* will be collected to assess inflammatory tone. Within two hours after blood drawing, samples will be centrifuged and hsCRP plasma levels will be extracted by the RLD. Plasma and whole blood will be stored at -80 °C for the remaining duration of the trial.

*Salivary cortisol* will be collected to assess the endocrine response to a laboratory stress-induction (see *socially evaluated cold pressor task* below). Four salivette tubes will be administered at T0 and T2. Specifically, saliva samples are collected 30–60 min prior to stress-induction, immediately after stress-induction, 30 min after stress-induction and 60 min after stress-induction. Saliva samples will be frozen and stored at -20℃ until analysis. After thawing, samples will be centrifuged at 3,000 rpm for 5 min. Salivary concentrations will be measured using commercially available chemiluminescence immunoassay with high sensitivity (Tecan - IBL International, Hamburg, Germany; catalogue number R62111).

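### The analysis named to test the effect of MBCT on hs-CRP decomposes an effect of stress on neurodegeneration; none of its four components estimates MBCT versus CAU on hs-CRP

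*Protocol article*

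**What the plan says.** The Objectives section asks, as secondary objective 2, whether the intervention "influences cerebral and biochemical markers of stress". Blood for hs-CRP "will be collected to assess inflammatory tone" (Secondary outcomes, Laboratory measurements), and Table 1 schedules it at the T0, T1 and T2 visits.

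The analysis is described in Statistical analyses, Laboratory measurements:

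- **Salivary cortisol:** the area under the curve is examined by TIME (T0, T2) and GROUP.
- **Hair cortisol:** levels "will be compared between T0, T1 and T2, and GROUP by means of LMM".
- **hs-CRP:** the sentence opens "To test the effect of MBCT on inflammatory tone" and continues "causal mediation analysis techniques will be used to decompose causal effects of stress on neurodegeneration into four components", namely "mediation (by inflammation) only, interaction (with inflammation) only, both, or neither".

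The opening paragraph of Statistical analyses adds two general rules: analyses follow intention to treat, and longitudinal data with more than two timepoints are analysed with linear mixed models.

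**The concern.** The aim and the method in the hs-CRP sentence belong to different questions. The aim is a treatment effect with hs-CRP as the outcome. The method is a four-way mediation analysis in which hs-CRP is an intermediate variable and neurodegeneration is the outcome. GROUP is not mentioned.

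An analyst who follows the sentence would produce four numbers, none of which says whether MBCT changed hs-CRP. Two things are at stake. The results could be presented as a test of an MBCT effect that they do not test. And if the GROUP comparison is specified only once data are in hand, its form is open to choice after the fact.

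This is not a detail that a condensed article leaves to a fuller document. A method is stated, and it does not answer the question attached to it.

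**Working it through.** The plan gives no figure to reproduce on this point. The check is whether any component of the named method equals the stated target.

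**1. Roles of the variables**

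| | Stated aim | Named method |
|---|---|---|
| Exposure | MBCT versus CAU | Stress |
| Outcome | hs-CRP | Neurodegeneration |
| Role of hs-CRP | Outcome | Mediator and effect modifier |

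**2. The four components.** Write the usual regression form, with exposure A moving from 0 to 1, mediator M = hs-CRP and outcome Y = neurodegeneration:

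- mean of M = b0 + b1·A
- mean of Y = t0 + t1·A + t2·M + t3·A·M

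With the mediator's reference value set to 0, the components are:

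- neither = t1
- interaction only = t3·b0
- both = t3·b1
- mediation only = t2·b1

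Each is on the scale of Y, neurodegeneration.

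**3. If stress is a measured variable.** Let MBCT shift stress by g, and so shift hs-CRP by b1·g. The quantity g appears in none of the four components. An illustration with assumed coefficients (b0 = 0, b1 = 0.4, t1 = 0.3, t2 = 0.3, t3 = 0.1; none of these comes from the protocol) gives:

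- neither = 0.30
- interaction only = 0.1 × 0 = 0
- both = 0.1 × 0.4 = 0.04
- mediation only = 0.3 × 0.4 = 0.12

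A simulation with these values and 400,000 subjects per scenario returned:

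| g | MBCT − CAU in hs-CRP | Neither | Interaction only | Both | Mediation only |
|---|---|---|---|---|---|
| 0 | 0.00 | 0.299 | 0.00 | 0.04 | 0.12 |
| −0.5 | −0.197 | 0.300 | 0.00 | 0.04 | 0.12 |
| −1 | −0.392 | 0.302 | 0.00 | 0.04 | 0.119 |

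The components do not move while the treatment effect on hs-CRP goes from nothing to about −0.39.

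**4. If stress stands for randomised GROUP.** Then A = GROUP and b1 is the MBCT − CAU difference in hs-CRP. It enters the components only as t3·b1 and t2·b1. If hs-CRP has no bearing on neurodegeneration (t2 = t3 = 0), both products are zero whatever b1 is. The mediator regression would yield b1 along the way, but the sentence does not name it as a result.

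**5. Comparison within the section.** Salivary and hair cortisol each have a stated GROUP comparison; hs-CRP has none.

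**The case against.** The strongest reply is the general rule at the head of Statistical analyses. hs-CRP has three timepoints, so the mixed-model rule could apply to it, and nothing says that the mediation analysis replaces a GROUP comparison. A reader might infer that the randomised comparison on hs-CRP is lost altogether; because of this rule, the document does not support going that far. But the rule mentions neither hs-CRP nor a GROUP contrast, and the specific sentence on hs-CRP names another method. At best the two places need reconciling.

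A second reply is that stress may be meant as the randomised contrast, since the Discussion presents the trial as a study of stress reduction. The text does not define how stress enters the decomposition. A reader might therefore infer that the result must be observational and confounded. That follows only if stress is a measured variable, which is the more natural reading but not a stated one. The illustration in step 3 assumes that reading; the mismatch itself does not, as step 4 shows.

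A third reply is that hs-CRP is assigned to inflammatory tone, while the stress biomarkers exemplified in the Discussion are cortisol and stress-related brain activity, so the tie to secondary objective 2 is loose. This is fair. The point rests on the aim written into the hs-CRP sentence itself, not on that objective.

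**Conclusion.** The concern holds as a mismatch between a stated aim and a stated method. Under either reading of stress, no component of the decomposition estimates MBCT versus CAU on hs-CRP, and no other passage states that comparison explicitly.

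Its reach is small: one of three laboratory markers, exploratory, with no effect on the primary HADS analysis or the sample size. A reader might want to express the loss as power for a GROUP test on hs-CRP. The document does not allow this: its baseline-to-follow-up correlation of 0.5 is assumed for HADS, and no correlation, variance or expected effect is given for hs-CRP.

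**What to change.** In Statistical analyses, Laboratory measurements, make two changes:

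1. State that hs-CRP at T0, T1 and T2 is analysed in a linear mixed model with GROUP, TIME and GROUP×TIME, in line with the hair cortisol comparison.
2. Move the four-way decomposition to a separate exploratory aim. Define its exposure, its outcome and the timepoint at which each variable is taken, and label it observational if the exposure is measured stress rather than randomised GROUP.

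The cost is a few lines of text and one further model. hs-CRP is already scheduled at all three visits, so no new data are needed.

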#### Neuroimaging

Neuroimaging data will be analyzed using neuroimaging software packages, such as FMRIB Software Library (FSL; https://fsl.fmrib.ox.ac.uk/fsl/) and statistical parametric mapping (SPM), as well as custom analysis scripts. Data will be pre-processed to remove motion and imaging artefacts; general linear models will be used to further clean the data from physiological noise and other nuisance signals. To test the effects of MBCT on cerebral markers of disease progression, we will explore the structural integrity of the substantia nigra and locus coeruleus as a function of TIME (T0 vs. T2) and GROUP (MBCT vs. CAU). Similarly, free water volume in the substantia nigra will be estimated by running a bi-tensor model on the diffusion weighted images [49]. Estimates will be compared between TIME and GROUP. The effects of MBCT on the cerebral stress response will be tested as follows: Subject specific connectivity estimates of relevant resting-state networks will be generated by first performing spatial group independent component analysis (ICA) in FSL-MELODIC (Multivariate Exploratory Linear Optimized Decomposition; www.fmrib.ox.ac.uk/fsl), and subsequently performing dual regression [50]. Stress-related networks (default mode network, salience network, executive control network) will be selected based on previous literature [51]. Resulting network connectivity estimates will be analyzed in a mixed-effects model with GROUP (MBCT vs. CAU), TIME (T0 vs. T2), STRESS (PRE vs. POST) and relevant interactions as fixed effects; a random intercept for SUBJECT will be included.

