**Methods:**

In a prospective randomized controlled trial (RCT), we investigate whether 8 weeks of MBCT, as compared to care as usual, can reduce symptoms of anxiety and depression in people with PD. We aim to include 124 PD patients, who experience mild-moderate symptoms of anxiety and depression, are eligible for magnetic resonance imaging (MRI) and naïve to mindfulness, and who have a disease duration ≤ 10 years. Every participant is followed for 12 months. Clinical and biochemical assessments take place at baseline (T0), after 2 months (T1), and after 12 months (T2); MRI assessments take place at T0 and T2. Our primary outcome is the total score on the Hospital Anxiety and Depression Scale (HADS) at T1, while correcting for the HADS score at T0, age, and gender. Beyond testing the effects of MBCT on symptoms of anxiety and depression in PD, we explore whether MBCT: (1) has an effect on motor symptom severity, (2) influences cerebral and biochemical markers of stress, and (3) leads to a change in biomarkers of PD progression.

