#### Baseline and follow-up assessment

At baseline (T0) and follow-up (T2), participants will visit the DCCN in a practically defined OFF-state (last levodopa intake ≥ 12 h prior to testing, 24 h for delayed release levodopa and dopaminergic agonists, 48 h for delayed release dopamine agonists) for a total of about 4 h, scheduled between 08:00 h and 15:00 h. Clinical, laboratory and neuroimaging assessments will be performed during the lab visit (see Table 1 for an overview of all outcome measures). All baseline assessments will take place within 8 weeks prior to the start of an intervention cohort; questionnaires will be filled out at home ON medication, within 1 week prior to the lab visit. The behavioral assessment will be completed within 1 week after the lab visit (ON medication). Assessments will typically be performed in the following order: neurological assessment and cognitive abilities (MDS-UPDRS, MoCA), laboratory assessments (blood, scalp hair), (f)MRI, additional motor symptom assessments (tremor, bradykinesia). Follow-up assessments will take place at least 12 months after baseline. Procedures during the T2 lab visit will fully match those of the participants’ baseline assessment.

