#### Neuroimaging

All subjects will be scanned on a SIEMENS Prisma or Prismafit 3T MRI system. Scanner type will be consistent within subjects. The following scans will be acquired:

*T1 weighted MPRAGE structural image* (TR: 2300ms, TE: 3.03ms, FA: 8 deg, TI: 1100ms, voxel size: 1.0 × 1.0 × 1.0 mm, FOV: 256 mm; acquisition time: 5m21s).Neuromelanin-sensitive *turbo spin echo T1 weighted image* to quantify structural integrity of the substantia nigra and locus coeruleus (TR: 890ms, TE: 13ms, FA: 120 deg, voxel size: 0.2 × 0.2 × 3.0 mm, FOV: 220 mm; acquisition time: 6m48s).*Diffusion weighted image* to quantify free water volume in the substantia nigra (TR: 3000ms, TE: 74.40ms, FA: 90 deg, voxel size: 2.0 × 2.0 × 2.0 mm, acceleration factor: 3, diffusion directions: 104, B-values: 1000 and 2000s/mm^2^, FOV: 210 mm; acquisition time: 5m30s).Resting-state BOLD EPI (functional MRI) images (eyes open, fixation cross) will be acquired twice: before and after stress induction (multi-band 3 multi-echo 3, TR: 1500ms, TE: 13.4ms / 34.8ms / 56.2ms, FA: 75 deg, voxel size: 2.5 × 2.5 × 2.5 mm, FOV: 210 mm, 400 volumes; acquisition time: 10m18s).

Participants’ stress-reaction will be investigated by means of the *socially evaluated cold pressor task* (SECPT) [33]. Resting-state functional MRI will be acquired before and after stress-induction (see imaging details above*)*. A researcher unknown to the participant will enter the room to perform the stress-induction task. The participant is asked to immerse their foot in a box of cold water (1.8–2.2℃) and to try keeping it in for three minutes, unless it is unbearable to continue. The participant is told that their facial expressions are evaluated during the task. The researcher is instructed to refrain from giving any positive feedback during the task and to try to keep a neutral facial expression. The second part of the stress-induction continues once the cold pressor test is over and the participant’s foot is covered with a towel. During the second part of the task, the participant is asked to alternatively cite the alphabet from the back and front (Z-A-Y-B-X-C etc.), as fast and as accurately as possible. If they are too slow, the researcher asks them to speed up. If they are incorrect, the researcher asks them to start from the beginning. This task lasts 3 min. Subjective stress levels will be collected before and after stress-induction on a 10-point scale [1 (not stressed at all) − 10 (very stressed)].

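### The resting-state model's only stated random effect is a subject intercept for four scans in two sessions, which costs power for GROUP×TIME×STRESS and can distort GROUP×TIME

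*Protocol article*

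**What the plan says.** In the Methods paragraph of the abstract, "MRI assessments take place at T0 and T2". The Neuroimaging section under secondary outcomes says that the resting-state images "will be acquired twice: before and after stress induction". The section on baseline and follow-up assessment adds that "Follow-up assessments will take place at least 12 months after baseline". So each patient contributes four scans, two in each of two sessions a year or more apart.

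The Neuroimaging section of the statistical analyses introduces the model with "The effects of MBCT on the cerebral stress response will be tested as follows". After GROUP, the specification reads "TIME (T0 vs. T2), STRESS (PRE vs. POST) and relevant interactions as fixed effects; a random intercept for SUBJECT will be included". On the random part it says nothing more: no session (SUBJECT×TIME) term, no SUBJECT×STRESS term and no other covariance structure. It does not list which interactions are meant and gives no variance components for the connectivity estimates.

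**The concern.** A model with only a subject intercept assumes that any two of a patient's four scans are equally correlated. Two scans from one visit share that day's positioning, arousal and state, and the patient's disease stage and treatment at that time. Scans a year apart do not. Patients may also differ in how strongly their networks react to the stressor, which links the two PRE scans and the two POST scans across sessions. A subject intercept represents neither. Both sources go into a single residual variance, which then serves as the error term for every within-subject contrast, although those contrasts have different true variances.

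What is at stake is the test of whether MBCT changes the cerebral stress response, part of a named secondary objective. That question is answered by whether the POST−PRE change shifts from T0 to T2 differently in the two arms, which is GROUP×TIME×STRESS. If its standard error is too wide, a real effect may be missed. The GROUP×TIME standard error, for a general change in connectivity, may be too narrow or too wide.

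**Working it through.** **Inputs.** From the article: two scans per session, two sessions, 1:1 allocation, two-sided alpha 0.05. The article states no power or error rate for this model. Its only sample-size figures are for the HADS: 70 per group; 70 × (1 − 0.5²) = 52.5, so 53; 53/0.85 = 62.35, stated as 62. The simulations therefore used 53 analysed patients per arm.

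Assumed, because the article does not give them: session variance q and subject-by-stress variance w, with residual variance set to 1. A session share s of within-subject variance (with w = 0) means q = s/(1 − s), so 25%, 50% and 75% give q = 1/3, 1 and 3.

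**Contrast variances.** Take scan = subject + session + subject×stress + residual, with complete data and contrasts scaled to unit length.

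- GROUP×TIME: true variance 1 + 2q
- GROUP×STRESS: true variance 1 + 2w
- GROUP×TIME×STRESS: true variance 1
- Subject-intercept model: the average of the three, P = 1 + (2/3)(q + w), used for all of them

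**Formulas.**

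- Type I error = 2·[1 − Φ(1.96·√(P / true variance))]
- Three-way power, for an effect that a correct test detects with 80% power = Φ(2.80 − 1.96·√P)

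**Results with w = 0.**

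| Session share | q | P | GROUP×TIME type I error | Three-way type I error | Three-way power |
|---|---|---|---|---|---|
| 0% | 0 | 1 | 5.0% | 5.0% | 80% |
| 25% | 1/3 | 1.222 | 9.3% | 3.0% | 74% |
| 50% | 1 | 1.667 | 14.4% | 1.1% | 61% |
| 75% | 3 | 3 | 20.0% | 0.1% | 28% |

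Worked row, q = 1: √(1.667/3) = 0.745 and 1.96 × 0.745 = 1.461, so GROUP×TIME type I error is 14.4%. √1.667 = 1.291 and 2.80 − 1.96 × 1.291 = 0.27, so three-way power is 61%.

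Simulation with 53 per arm (8,000 runs per setting) agrees. At q = 1 it gave 14.1% GROUP×TIME type I error and 61% three-way power. When each contrast was tested against its own variance, type I error was about 5% and three-way power about 80% at every q tried.

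**When w is not zero.** GROUP×TIME is anticonservative only if 1 + 2q > 1 + (2/3)(q + w), which reduces to q > w/2. With w = 1:

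| q | P | GROUP×TIME type I error | Three-way power |
|---|---|---|---|
| 0.25 | 1.833 | 3.0% (conservative) | 56% |
| 0.5 | 2 | 5.0% | 51% |
| 1 | 2.333 | 8.4% | 42% |

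The three-way test loses power in every row, because P exceeds 1 whenever q or w is positive.

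**Would a session intercept alone repair it?** With SUBJECT×TIME added but not SUBJECT×STRESS, the within-session error averages 1 + 2w and 1, giving 1 + w. At q = w = 1, three-way power is Φ(2.80 − 1.96·√2) = 51% (53% by simulation), against about 80% for the per-patient difference of differences. At q = 0.25, w = 1, simulation gave 57% with the stated model, 56% with the session intercept added and 80% with the difference of differences.

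**The case against.** **Session variance may be small.** The article keeps scanner type constant within patients, matches T2 procedures to baseline, tests in the OFF state and removes motion and physiological noise. These steps should reduce q, and nothing in the article supports the 75% case in particular. They do not make q zero, because patient-specific change over a year in a progressive disease is itself SUBJECT×TIME variance. The range stands as an assumption.

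**GROUP×TIME need not be inflated.** A reader might infer that the stated model always gives false positives for GROUP×TIME. The article does not support that: it gives neither q nor w, and the direction reverses when q is below w/2. Nor does it name GROUP×TIME as a test of interest. This objection stands.

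**The key interaction is inferred.** The article speaks only of relevant interactions. That is correct, but no other term in the model expresses an effect of MBCT on the change in stress response.

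**Tremor.** It is tempting to extend the point to the tremor model, where conditions are likewise nested in visits: "We will also explore tremor amplitude as a function of GROUP (MBCT vs. CAU), TIME (T0 vs. T1 vs. T2) and CONDITION". The article calls that analysis a linear mixed model and states no random structure for it, so there is no stated error to correct.

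**Other terms may be added.** Saying that a subject intercept is included does not say that it is the only term, and a fuller analysis plan may add more. The point therefore concerns the structure the article chose to state, which does not match the design it describes.

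**Conclusion.** The point holds as a minor one. If the stated random structure is followed, GROUP×TIME×STRESS is conservative and loses power for any positive session or stress-reactivity variance. With w = 0 and assumed session shares of 25%, 50% and 75%, power falls from 80% to about 74%, 61% and 28%. GROUP×TIME type I error is about 9%, 14% and 20% at the same shares, but this inflation is conditional on q > w/2. The sizes rest on the assumed variances, on complete data and on reading the three-way interaction as the test of the stress response.

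For that test the error is lost power, not false claims. The analysis is exploratory. A reader should not infer any effect on the primary HADS ANCOVA or the sample size, since neither uses this model.

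**What to change.** Test GROUP×TIME×STRESS by comparing the arms on the per-patient contrast (POST − PRE at T2) minus (POST − PRE at T0), and test GROUP×TIME on the per-session means. Each effect is then judged against its own between-patient variance.

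If the mixed model is kept, for instance to use patients with incomplete scans, include both SUBJECT×TIME and SUBJECT×STRESS random effects beside the subject intercept. SUBJECT×TIME alone does not restore three-way power if patients differ in stress reactivity. It would also help to name GROUP×TIME×STRESS as the interaction of interest.

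The cost is a change to the model specification, with no new data or visits. The article expected recruitment to finish by August 2025, with T2 a year after baseline, so on that timetable the last T2 scans fall around August 2026. The change should be fixed before the imaging data are analysed.
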